#### Qualitative

*Trial participants*,* partners*,* and peers*: A sub-sample of trial participants selected for variability in reported short-term subjective and objective effectiveness and quantitative acceptability will be invited for an in-depth interview on user experience (i.e., acceptability, stigma, and quality of life) after clinic-based and/or community-based usage. This purposive and criterion sampling will allow us to examine clinical significance (i.e., what do users perceive is a meaningful amount or percentage reduction in leakage with use of cup/cup+) and identify who might be an optimal user of the cup/cup+ (including based on anatomical characteristics). In addition, and as appropriate, we will ask each recruited participant if we can talk to a male partner, another family member, or a peer to ask related questions about acceptability, as male engagement and family member support could shape interaction with women’s health services [69–71] and their decision to use the cup/cup+. *Providers*: Diverse implementers will be recruited for in-depth interview on implementer acceptability, which will inform us on how best to identify and address potential implementation challenges, beyond user characteristics. Qualitative participants may receive an additional ~$5-15 USD.

### Clinical trial procedures

#### Clinic-based procedures

After consent and enrollment of a participant, as well as baseline measurement of leakage, clusters of approximately 4 to 10 participants enrolled around the same time will be block randomized using REDCap software and the participant clusters will be allocated to one of two groups (Fig. 2). Women who are menstruating at the time of baseline measurement or expect to begin menstruation during the week of initial data collection will be noted as such and expected additional volume of blood leakage will be accounted for during data analysis to reduce measurement error.

##### Randomization

Participants will be group randomized to one of two groups of varying sequences of 24 h of either leaking freely, cup, or cup+ (Fig. 1). This crossover design uses participants as their own controls, reduces the risk of confounding due to intervention order, and captures two estimates of leaking freely (group 1) and cup (group 2) to assess any sequential differences in leaking variability. Based on the intervention mechanism of effect and lack of carry-over effect, no washout period is required between sequences. As the clinic-based component of the trial will be implemented in small groups prioritizing feasibility and quality control, randomization at the group level is preferred and will be implemented by the study data manager at the time each cohort is recruited using coin toss. The study physician and nurse will enroll participants and inform them of the treatment group for immediate participation.

#### Participant education

Once enrolled, participants will receive education, counseling, and practice on insertion, use, removal, and hygiene practices of the vaginal cup and cup with tubing per group sequence [72]. The study nurse will teach subjects how to place and remove the cup from the vagina and wear the cup with tubing connected to a collecting bag. Culturally-appropriate pelvic models will be used for education, demonstration and review. Study staff will instruct women to remove and reinsert the cup as they need or desire, supply detailed instructions about when and how to seek medical advice or help, and address participant questions [73]. Participants will also be taught how to wash the cup using soap and water and the leg bag and tubing using water and vinegar or bleach. The cup can be air dried or wiped dry. Participants will have ample opportunity to practice insertion, removal, and washing of cup by themselves, as well as the attachment, removal, emptying, and washing of the tubing and collecting bag. The importance of hand hygiene will be emphasized [72]. Study staff will explain that women should feel free to remove and reinsert the cup as they feel is appropriate. If they think the cup is getting full, which they might suspect if starting to leak, they will be encouraged to empty the cup using the valve or via removing the cup, empty and re-insert. Participants will be encouraged to ask questions during this discussion and can access supportive assistance from the study nurses. Participants will be counselled to drink enough water to allow the free flow of colorless, odorless urine [73]. All instruction and data collection will occur in the participant’s preferred local language. Given expected literacy constraints, education and training will emphasize verbal and visual strategies. Still, brief written and pictorial materials will be offered to participants for their ongoing reference, with sensitivity to protecting women’s fistula concealment, their use of the cup/cup+, and their participation in the trial.

##### Data collection

Data will be collected within the clinic-based phase via questionnaire, clinical exam (by a physician), clinical checklist (by nurse/midwife), pad test, and observation (Fig. 1; Table 2). At baseline, a gynecological exam will be carried out as potential participants are being screened and, once enrolled, the baseline questionnaire will be administered. Data will be directly entered into the REDCap mobile app to facilitate data privacy and quality. Next, all participants will be provided disposable pre-weighed adult pads or diapers for the first six hours of each treatment assignment while carrying out typical activities daily living activities on the ward. Six hours was deemed to be a clinically significant amount of time to provide women some relief from their leaking to allow them to engage in social activities or sleep uninterrupted. Additionally, six hours will likely provide those in the cup + assignment the opportunity to fill and then empty their leg bag. Lastly, six hours was deemed logistically feasible for data collectors (i.e., at the start and end of their shift). When assigned to cup or cup+, participants will also insert and wear the respective cups. Women will be encouraged to void ‘normally’ if they sense urgency and instructed to change their diapers as frequently as they see fit when they feel dampness and to deposit the used diapers into a personal plastic Ziplock bag that is then sealed until study staff can record the weight of the wet diapers. At the end of the first six hours of each treatment assignment, the weight of the participant’s assigned dry diapers will be subtracted from that of the wet diapers to calculate the volume of urine leaked, and participants will be asked questions regarding perceived effectiveness. Participants will continue with their assigned treatment until 24 h of use, at which time another questionnaire and a clinical checklist to note any adverse events will be administered by the study physician or nurse/midwife.

**Table 2 Tab2:** Quantitative study measurements, data sources, and timing of assessment

Category	Measure	Data Source^a^	Clinic				Community		
			0h	6h	24h	4d	1m	2m	3m
Outcome variables									
Quality of life ^b,c^	Quality of life (Post-fistula repair reintegration instrument)^*92*^	PS	●				●	●	●
Urine leaked (observed) ^c^	Pad weight; number of pads used, food and fluid intake, voiding	PT, TM		●					
Urine leaked (perceived) ^c^	Perceived difference in leakage (cup, cup+, leak free)^90,91^	PS		●	●		●	●	●
Acceptability (patient, family, clinician) ^c^	Ease, comfort, interference, likelihood to use or recommend	PS		●			●	●	●
	Barriers to use, concerns, use decision-making process	PS				●			
**Covariates**									
*Patient-related*									
Socio-demographics ^c^	Age, education, socio-economic status	PS	●						
Obstetric history	Parity, delivery type, timing of fistula, repair attempts	PS	●						
Reproductive health ^c^	Menstruation, pregnancy status	PS	●		●		●	●	●
Other health/functional ^b,c^	Stigma ^*93*^	PS	●				●	●	●
*Fistula-related*									
Fistula characteristics ^b,c^	Fistula classification, distance from external urethral orifice	CE	●	●					
Physical signs and safety ^c^	Vaginal mucosa, vulvar dermatological, fistula etiology	CC		●	●	●			●
Physical symptoms ^c^	Fistula-related symptoms (incontinence severity, pain, mobility)	PS	●				●	●	●
Fistula management practices, time, costs ^c,d^	Time and methods used for managing leakage, pain; cost of usual odor or leakage management,^94^ participation in social activities	PS	●		●		●	●	●

Note: ^a^Data Sources include clinical checklist (CC), clinical exam (CE), patient survey (PS), pad test (PT), and time motion (TM). ^b^Measures demonstrated to be valid in this population. ^c^Measures previously used by the research team in this population. ^d^Individual cost data will include time/opportunity costs to visit clinic, payments for management time, equipment, and opportunity costs of family/ friend caretakers

### Community-based procedures

On the last clinic day, participants will be individually randomized to use of cup or cup + at home for up to three months (see Randomization; Fig. 1) for community-based assessment of the longer-term effectiveness, acceptability of the cup and cup+, and material and opportunity costs to non-surgical fistula management. We will assess perceived change in leakage associated with cup/cup + use, quality of life, acceptability and adherence via survey and clinical checklist administered at one and two months either over the phone as we have done in prior studies [63, 74] or in-person per participant and data collector preference, and semi-structured interview and clinical exam in-person at three months. Participants will be provided with airtime to ensure their ability to contact study personnel.

### Study termination

Participants will be free to discontinue use of any individual intervention assignment or withdraw from the trial completely at any point throughout the study. Criteria for study-initiated discontinuation include user perception of and/or clinical observation of adverse events such as significant pain. Study participation will not delay participant access to fistula surgery; if active study participants are called for fistula surgery, they will complete research activities through the time of surgery at which point they will be withdrawn. Outcomes will be recorded for those who discontinue or deviate from the intervention protocol, including reason for discontinuation or deviation and length of use. Participants will receive a clinical exam at the time of discontinuation or deviation.

### Qualitative study procedures

Qualitative assessment among a purposively selected sub-sample of trial participants, their partners, and peers (*n* = 30) will provide a more in-depth understanding of user experience, including acceptability, stigma, and quality of life. Interviews will be informed by the Consolidated Framework for Implementation Research (CFIR) and the Theoretical Framework of Acceptability (TFA), [58, 75] and the interview guide will be further adapted during the clinic-based assessment phase and by the community advisory board. The interview will occur at a mutually agreed-upon location for participant and researcher where the researcher can maintain appropriate privacy for the participant. Interviews will be audio recorded with permission. For trial participants, this may be at the clinic during their final study follow-up visit at up to three months or at their home, as per their preference. For implementers, this may be at their place of work or another convenient location. Interviewees will be remunerated for their time.

The acceptability survey captures Theoretical Framework of Acceptability constructs relevant for user acceptability: attitude, burden, perceived effectiveness, ethicality, intervention coherence, opportunity costs, and self-efficacy (Table 2) [58]. Interview questions will include sensitizing concepts from the five CFIR domains given their potential impact on evidence-based intervention implementation [75]. Most relevant domains for trial participants may include: intervention itself (intervention source, relative advantage, adaptability, trialability, cost, complexity) and outer setting for implementation (patient needs and resources). Most relevant domains for implementers may include: individuals involved in implementation (knowledge and beliefs about the intervention, self-efficacy), the inner and outer setting (structural characteristics, external policies, culture, networks, communications), and the process by which implementation occurs (planning, engaging, executing, reflecting, evaluating). We will also explore recently proposed adaptations to the CFIR to increase compatibility of use for lower-resource settings including to account for systems-level determinants operating independently of the implementing organization and 11 novel constructs augmenting the utility and comprehensiveness [76]. This stakeholder group will also engage in creating a list of potential implementation strategies to improve fit of implementation for this context.

### Costing study

Using time motion study (TM)^77^ and micro-costing methods, we will longitudinally survey all trial participants (*n* = up to 100) while in the facility and during community-based follow-up on fistula management practices to estimate direct costs (medical and nonmedical) and indirect costs (productivity) from the patient perspective. We will compare fistula management costs between cup, cup+, and usual non-surgical methods to inform the social impact of fistula management and future cost-effectiveness assessment. While it is often recommended that time motion is conducted with an external observer, [77] the sensitivity and stigma surrounding non-surgical fistula management makes the employment of an external observer of personal hygiene behavior inappropriate. Nevertheless, it is critical to capture individual indirect cost of non-surgical fistula management and how the cost may vary across interventions thus we rely on participant self-report of non-surgical fistula management in the community. Potential for bias will be minimized through use of standard questions focused on 24-hr recall. During community-based follow-up by the research assistants, multiple assessment points will allow us to observe change over time as well as understand the influence of community-level factors (e.g., distance to latrine, accessibility of water) on non-surgical management.

Cost data will be captured from all trial participants. Participants will self-report estimates of usual time and resources spent managing incontinence and, within the facility-based procedures, time spent managing incontinence over the 24 h periods assigned to leaking freely, using cup, and using cup+. During community-based follow up, these individuals will be surveyed with the same questions monthly through three months [78, 79]. We will micro-cost fistula-related resources using published prices [80]. Community-administered surveys will include measures of cost for supplies related to fistula management and productivity lost; we will supplement the TM data with data on opportunity costs collected within our acceptability assessment (Aim 2). Clinic treatment cost (e.g., human resources and provider time effort) will be collected from facility managers. In addition, average sales and wholesale prices of supplies will be combined with utilization patterns captured during TM to calculate fistula management cost and to supplement participant-reported costs. The three data sources will comprehensively capture the range of fistula management costs. To minimize discrepancy, we will provide detailed activity categories in our survey (e.g., inserting/removing cup, washing, etc.). To maximize rigor, participants will be trained on 24-hour activity reporting during their time at the facility.

### Data analysis

#### Quantitative

We will assess missingness and normality of variables; multiple imputation (> 5% missingness), transformation and other techniques will be considered. Data will be summarized descriptively. Intention-to-treat will be the primary analysis. Study data management procedures are available upon request by the study team.

#### Effectiveness outcomes

##### Urine leakage

We will estimate the effectiveness of each intervention (cup and cup+) on six-hour urine leakage through linear mixed-effects regression analysis with subject-specific random intercepts. This approach is the superior approach for maximizing statistical power as it uses all collected data to simultaneously model the treatment and period effects (carry-over effects are not anticipated for this trial); allowing us to simultaneously model our three primary comparisons of cup vs. leak freely, cup + vs. leak freely, and cup vs. cup +  [81, 82].

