Cross-over trial designs provide greater efficiency than parallel designs due to within-subject treatment comparisons where each subject serves as their own control, resulting in lower sample size requirements for statistical power. Our sample size of up to 100 participants (400 observations) is calculated to assess: (1) a ≥ 65% reduction at six hours in observed urinary leakage, and (2) a mean 40% quality of life difference at three months between the cup and cup+ (measure range 0-100; Supplementary Figures). We expect > 80% retention over three months study follow-up based on our research with 12-months follow-up with 98% retention with this target population in Uganda^63^ and 3-months follow-up in Ghana with 84% retention, [64, 65] and have inflated our target sample size conservatively.

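### Sequences are allocated to whole cohorts, but the primary leakage model has only subject intercepts, so any cohort-by-day correlation is missed, chiefly for cup vs cup+; the two accounts of the allocation mechanism also conflict

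*Protocol article*

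**What the plan says.** **Unit of allocation.** Two sections of the Protocol article make the cohort the unit. Under Clinic-based procedures, "the participant clusters will be allocated to one of two groups". Under Randomization, "Participants will be group randomized to one of two groups of varying sequences", and group-level allocation is said to be preferred for feasibility and quality control.

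**Mechanism.** The same two sections differ here. Clinic-based procedures: "clusters of approximately 4 to 10 participants enrolled around the same time will be block randomized using REDCap software". Randomization: allocation "will be implemented by the study data manager at the time each cohort is recruited using coin toss". The Abstract and Study design also speak of block randomisation.

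**Primary leakage model.** The Urine leakage section specifies "linear mixed-effects regression analysis with subject-specific random intercepts", used to "simultaneously model the treatment and period effects". It names three primary comparisons: cup vs leaking freely, cup+ vs leaking freely, and cup vs cup+. It names no cohort or cohort-by-period term and no cluster-robust variance.

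**Sample size.** Up to 100 women give 400 observations. For observed leakage the analytical sample size is 50 (ANCOVA, two-tailed alpha 0.025, power 0.8 to 0.9). No intracluster correlation or design effect is mentioned.

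**Interim look.** Data and safety monitoring plans an interim analysis at 50 women, and Stopping rules sets a boundary of p<0.001.

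**The concern.** On the natural reading of these sections, the women of a cohort stay on the ward together and move through the same sequence on the same days. Whatever raises or lowers leakage on one of those days can then move all their pad weights together, in step with the condition they share. The article itself points to candidates: the study supplies food and water, staff counsel women on fluid intake, and pads are weighed over one six-hour window on the ward.

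The subject intercept removes what is stable in each woman. It does not remove what a cohort shares on one day. Cohorts are recruited at different times, so a period effect common to all cohorts captures only the average first, second, third or fourth day, not the particular day a cohort experienced. Women may then be counted as independent replicates when they are not, with intervals that are too narrow and false-positive rates above nominal, at the interim look as well.

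The conflict over the mechanism is a separate defect. A reader cannot tell how sequences were generated, so cannot judge concealment or restriction.

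**Working it through.** **Inputs from the Protocol article:** cohorts of about 4 to 10 women; up to 100 women, hence 100/10 = 10 to 100/4 = 25 cohorts, or about 14 of 7; two-sided alpha 0.025 for leakage (given in the sample size text); planned reduction of at least 65%; feasibility leakage 63.2 ml (SD 49.2); interim boundary p<0.001.

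**Assumed, because the documents give no value:** ρ, the share of within-woman variance common to a cohort on one day, at 0.05 and 0.10.

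**1. The plan's N of 50.** Take the 65% reduction against leaking freely: difference 0.65 × 63.2 = 41.1 ml, SD 49.2. Using these feasibility figures is an assumption. Total N = 4 × [49.2 × (2.241 + z_power)/41.1]², multiplied by (1 − r²) for a covariate correlation r. With r = 0 this gives 54.5 at 80% power and 71.2 at 90% before rounding (56 and 72 in equal groups). N = 50 needs r of about 0.29 and 0.55 respectively. The article does not state r, so 50 is plausible but cannot be verified.

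**2. What cancels.** Write a woman's leakage as treatment + period + woman + cohort + (cohort × day) + residual. In a difference between two of her days, the woman and cohort terms drop out. The difference between the two cohort-day terms stays and is the same for all m women.
- True variance of the cohort's mean difference: 2(σ²_cd + σ²_e/m)
- Variance the model assumes: 2(σ²_cd + σ²_e)/m
- Ratio, with ρ = σ²_cd/(σ²_cd + σ²_e): **1 + (m − 1)ρ**

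**3. Size.** Actual type I error = 2[1 − Φ(z/√DE)], with z = 2.241 for alpha 0.025.

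| Women per cohort | ρ | Design effect | Type I error, nominal 0.025 | N = 50 becomes |
|---|---|---|---|---|
| 4 | 0.05 | 1.15 | 0.037 | 58 |
| 4 | 0.10 | 1.30 | 0.049 | 65 |
| 7 | 0.05 | 1.30 | 0.049 | 65 |
| 7 | 0.10 | 1.60 | 0.076 | 80 |
| 10 | 0.05 | 1.45 | 0.063 | 73 |
| 10 | 0.10 | 1.90 | 0.104 | 95 |

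For the p<0.001 boundary (z = 3.291) and m = 7: 3.291/√1.3 = 2.886, giving 0.0039; 3.291/√1.6 = 2.602, giving 0.0093. This assumes the interim test uses the same leakage model. About 50/7 ≈ 7 cohorts would support that look.

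**4. Check by simulation.** The subject-intercept model with fixed treatment and period effects was run 2,000 times per setting at nominal 0.025. Two versions of the four-day sequences were assumed, because the participant flow figure is not shown.
- Stable cohort effect only: type I error about 0.02 to 0.03, ratio of true to model standard error about 1.0.
- 14 cohorts of 7: about 0.045 to 0.06 (ρ = 0.05) and 0.074 to 0.087 (ρ = 0.10).
- 10 cohorts of 10: about 0.056 to 0.072 and 0.106 to 0.116.
- 25 cohorts of 4: about 0.036 to 0.044 and 0.042 to 0.051.

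The simulation agrees with the formula.

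**5. Interval width.** √1.3 = 1.14 and √1.6 = 1.26, so correct intervals are about 14 to 26% wider at m = 7.

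**The case against.** **The effect may be absent.** This stands. A reader might infer that all three contrasts are certain to have intervals that are too narrow. The documents do not support that: they give no cohort-by-day correlation, and stable cohort differences do no harm.

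**Some shared influences are measured.** Table 2 records food and fluid intake and voiding with the pad test, and secondary analyses will examine potential confounders. Adjustment could absorb part of a shared day effect, but the primary model as described names no such covariates.

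**The contrasts are not equally exposed.** This stands too. Against leaking freely the planned reduction is at least 65%, and even the largest inflated N in the table (95) is within the 100 women planned. Cup vs cup+ has no such margin, and the article gives no leakage sample size for it.

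**The SAP may settle it.** It may add detail, but the article does not leave the random-effects structure open; it names it and defends it on grounds of power.

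**The coin toss is not shown to bias anything.** A reader might infer that chance imbalance between sequences, overall or within a site, biases the result, or that the tosses went unrecorded. The pooled model includes period effects, so a 10:4 split of 14 cohorts costs efficiency (4 × 10 × 4/14² = 0.82), not validity. Nothing in the article says the result of a toss is not recorded. Block randomisation could also mean that the cohort is the block. Even so, REDCap and a coin toss remain two different mechanisms.

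**Conclusion.** The concern holds, conditionally. The primary leakage model does not reflect that cohorts, not women, are allocated to sequences. The consequence depends on one quantity the documents do not give. At a cohort-by-day correlation of 0.05 to 0.10 with 7 women per cohort, a nominal two-sided 0.025 test runs at about 5 to 8%, and a p<0.001 look at about 0.4 to 0.9%. Smaller cohorts fare better and larger ones worse. The figures also rest on the reading that a cohort's women share each condition on the same day, and on assumed sequences in the simulation.

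The practical risk is an overconfident statement about cup vs cup+. The conclusions against leaking freely are unlikely to change. The home-use phase is individually randomised and is not affected.

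The conflict between REDCap block randomisation and a coin toss is on the face of the document and needs correcting whatever the correlation proves to be.

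**What to change.** **Analysis.** Add a cohort-by-period random effect to the primary leakage model and use small-sample degrees of freedom (Kenward-Roger). A cohort-level robust variance or a cohort-level randomisation test, each with small-sample correction, would also serve. A cohort intercept alone would change little. Give an analysis of cohort-level summaries as a sensitivity analysis. Use the same model at the interim look, and make the change before that look.

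**Allocation.** Reconcile Clinic-based procedures with Randomization and state one cohort-level mechanism, for example a concealed, pre-generated list in REDCap with varying block sizes. Fixed blocks of two cohorts would be a poor choice: conditions are visible and the staff who enrol women also tell them their group, so every second allocation could be foreseen. Report how the cohorts already enrolled were allocated; the article gives 16 completers at the time of writing.

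**Cost.** One model term, one allocation list and a paragraph of text. Intervals widen by about 14 to 26% at the assumed correlations with 7 women per cohort, and somewhat more with few cohorts once small-sample degrees of freedom are used. Some power is lost for cup vs cup+, and this should be acknowledged in the plan.
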